### The Project’s Ambition

The S4R project will advance the current state of the art by developing, implementing, and evaluating a research-based digital S4R Toolbox to support health care leaders in promoting resilient performance and mental well-being among health care workers and informal caregivers in European and Australian older adult care. The S4R Toolbox will be an online platform that provides leaders with effective individual and collaborative tools designed to support leadership action. Its focus will be on creating a sound system in which leaders are competent and able to adapt to workforce needs and suggestions, with the potential to improve working conditions, mental well-being, resilient performance, and reduce stress and burnout. The project also aims to build an understanding of how to adapt to change, respond to adverse events, and innovate under increasingly demanding circumstances. The ambition is to generate an “exponential” effect, whereby implementing the S4R Toolbox through health care leaders improves conditions for many health care workers and informal caregivers in older adult care. The S4R project envisages a digital toolbox with 3 separate tools (see Figure 1):

A Mapping and Identification Tool that will provide leaders with a holistic understanding of the current status of the organization by integrating the perspectives of health care workers and informal caregivers.A Reflection and Education Tool that will provide a contextual understanding of “work-as-done” rather than “work-as-imagined” and educational components to identify successful adaptations and solutions for reducing capacity-demand gaps.A Reorganization Tool that will be designed to support reframing by identifying which practices to preserve, implement, or de-implement, resulting in detailed action plans (see Figure 1).

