### Co-Design of the S4R Toolbox and Prototype Testing Phase

#### Overview

The second phase (WP3) will lead to the development of a digital S4R Toolbox for leaders to promote resilient performance and mental well-being among health care workers and informal caregivers. WP3 begins in month 5 and continues through month 30. The features and content of the S4R Toolbox will be developed based on findings from the first input phase, systematic literature reviews, and cross-country qualitative and quantitative data collection. Cross-country data from diverse settings will be used to provide an understanding of factors and challenges that are relevant across settings (residential care homes, home care services, and the hospital-to-home interface) and target groups (leaders, health care workers, and informal caregivers), ensuring that the S4R Toolbox provides value across the included older adult care settings. The development phase applies an iterative co-design methodology using an Agile software development process [33], in which a development team continuously develops the content and features of the S4R Toolbox by organizing 8 collaborative workshops (6 national and 2 transnational) with a co-design panel consisting of consortium partners and collaborators, as well as representatives of the target groups (3-5 health care leaders, 3-5 health care workers, and 3-5 informal caregivers), to ensure relevance and usability.

The S4R Toolbox includes 3 tools: (1) Mapping and Identification Tool (to increase awareness), (2) Reflection and Education Tool (to increase understanding), and (3) Reorganization Tool (to support reframing; Figure 1). While the S4R Toolbox is intended for leaders, the tools rely on the involvement of different stakeholders, including health care workers and informal caregivers, to ensure collaboration across organizational levels and stakeholder groups. All test sites will implement and evaluate the S4R Toolbox through a 1-year intervention program. The S4R Toolbox aims to bring about organizational- and system-level changes through leaders as change agents to improve working conditions for frontline health care workers and informal caregivers. Accordingly, the intervention requires sufficient time for these changes to take place.

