#### S4R Intervention Design Development Phase

Given the pace of work and the stressful environment of older adult care, the intervention design will be aligned with everyday work to reduce the likelihood that leaders will perceive the intervention as an additional stressor [34]. The S4R intervention will consist of 3 phases, each corresponding to 1 of the 3 tools in the S4R Toolbox. During each phase, frontline leaders will engage with different elements of the tool and participate in different activities (see Multimedia Appendix 3). The implementation of the intervention is planned to take 12 months. Six local learning collaboratives (including consortium researchers and co-researchers from the clinical setting) will be established, 1 in each European partner country, in addition to 1 principal learning collaborative comprising representatives from all 6 local learning collaboratives. Australia will have a separate learning collaborative because of time zone differences.

For each country, a designated intervention team consisting of consortium partners will be formed. The teams will be responsible for administering the local learning collaborative and coordinating the overall implementation activities throughout the intervention in their respective countries.

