#### Cost-Effectiveness Analysis

Cost-effectiveness analysis will be conducted only for the cRCT study design (Norway and Finland).

The primary outcome will be SWEMWBS, with effectiveness assessed using the same methods described in the previous section.

The costs of the intervention will be based on the time spent by leaders, health care workers, and researchers implementing the S4R Toolbox. The learning collaboratives support the leaders and are therefore expected to influence the effectiveness of the Toolbox. The cost data will be based on the following:

Minutes that health care workers use the Toolbox (data source: log files from the digital Toolbox).Hours that leaders and health care workers spend in meetings discussing the themes of the Toolbox and planning deimplementation or other workplace changes (data sources: learning collaborative meetings and interviews with leaders).Hours that leaders and researchers spend participating in local learning collaboratives (data source: notes/minutes from the learning collaboratives, including time and participants).The time spent by health care workers, leaders, and researchers will be valued using nationally representative wages and social security contributions.

The time horizon for the analysis is 1 year; therefore, no discounting will be applied. The analysis adopts the perspectives of 2 funders: the participating organizations, which cover the costs of leaders’ and health care workers’ time, and the S4R project funding organization (EU), which covers the costs of researchers’ support for implementing the Toolbox.

We use intention-to-treat based analyses and evaluated the incremental net monetary benefit of the Toolbox compared to no Toolbox ("practice as usual"). We evaluated incremental net monetary benefit (NMB) in comparing the alternatives. NMB is calculated by multiplying the observed effects by the decision-makers’ willingness to pay, λ, for an extra unit of effectiveness, and then subtracting the observed cost [37,38]. As the willingness to pay for one extra unit of effectiveness in SWEMWBS is unstated, we use a range of values.

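### The cost items count leaders' time only in meetings and learning collaboratives, so leaders' own Toolbox use outside those sessions would go uncosted if the list is applied as written

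*Protocol article*

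**What the plan says.** All references are to the protocol article. The Cost-Effectiveness Analysis section opens with the scope: "The costs of the intervention will be based on the time spent by leaders, health care workers, and researchers implementing the S4R Toolbox". It then lists three sources of time data:

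1. Platform time: "Minutes that health care workers use the Toolbox (data source: log files from the digital Toolbox").
2. Meetings: "Hours that leaders and health care workers spend in meetings discussing the themes of the Toolbox and planning deimplementation or other workplace changes", taken from learning collaborative meetings and interviews with leaders.
3. Learning collaboratives: "Hours that leaders and researchers spend participating in local learning collaboratives", taken from the notes of those sessions.

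The valuation sentence that follows names all three groups again. The perspective is that of two funders, one of them being "the participating organizations, which cover the costs of leaders’ and health care workers’ time".

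On who uses the platform, the overview of the co-design phase says: "While the S4R Toolbox is intended for leaders, the tools rely on the involvement of different stakeholders". The section on the project's ambition says: "The S4R Toolbox will be an online platform that provides leaders with effective individual and collaborative tools designed to support leadership action". The intervention design section says: "During each phase, frontline leaders will engage with different elements of the tool and participate in different activities". The cRCT section defines the two arms by whether health care leaders do or do not implement the Toolbox.

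**The concern.** The scope sentence and the itemized list do not match. The scope includes leaders without restriction, but the list reaches them only through meetings and collaboratives. The one item that measures time on the platform is confined to health care workers, who are not the group for whom the platform is primarily built. A leader who reads the Tool 1 reports alone, prepares a Tool 2 module or drafts a Tool 3 action plan at a desk generates time that no item collects.

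The missing cost would arise in one arm only, so the error would have a known direction and would favour the Toolbox. Neither the range of willingness-to-pay values nor the WELLBY sensitivity analysis would expose it, because both change how the effect is valued and leave the cost as it is.

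**Working it through.** The article gives no hours, wages or net-benefit figure, so there is no stated result to reproduce. The check has three parts.

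**1. Whose time does each item count?**

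| Item | Leaders | Health care workers | Researchers |
|---|---|---|---|
| Platform minutes (log files) | no | yes | no |
| Meeting hours | yes | yes | no |
| Learning collaborative hours | yes | no | yes |

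The scope sentence, the meetings item, the valuation sentence and the perspective sentence all name leaders and health care workers as separate groups. Reading the log-file item as silently including leaders would go against that usage. The intervention design section also distinguishes leaders' engagement with the tool from their participation in activities. The cell for leaders' platform time is therefore empty, except where that time falls inside a session counted by the other two items.

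**2. What does the empty cell do to the result?**

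The article defines net monetary benefit as effect times willingness to pay (λ), minus cost. Between arms:

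INMB = λ × ΔE − ΔC

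Let C_L be the cost of leaders' Toolbox time outside counted sessions. It is zero in the control arm, which has no Toolbox. If C_L is left out of the intervention arm, the cost difference used is ΔC − C_L, and

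INMB as computed = λ × ΔE − (ΔC − C_L) = INMB + C_L

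The overstatement is C_L and does not depend on λ.

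**3. How large could it be?**

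Inputs from the cRCT section: 30 clusters with equal allocation, hence 30 / 2 = 15 intervention clusters, and about 30 workers per cluster. The time horizon in the cost section is 1 year. The number of leaders per cluster and their hours are not given, so both are assumptions.

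With one leader per cluster and 1-4 hours per month:

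- Per cluster: 1 × 1 × 12 = 12 hours to 1 × 4 × 12 = 48 hours
- Over the arm: 15 × 12 = 180 hours to 15 × 48 = 720 hours
- Per worker: 12 / 30 = 0.4 hours to 48 / 30 = 1.6 hours

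With a wider assumed range of 1-2 leaders per cluster and 6-52 hours per leader over the year:

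- Per cluster: 1 × 6 = 6 hours to 2 × 52 = 104 hours
- Over the arm: 15 × 6 = 90 hours to 15 × 104 = 1,560 hours
- Per worker: 6 / 30 = 0.2 hours to 104 / 30 = 3.5 hours
- At an assumed 30-60 currency units per hour: 0.2 × 30 = 6 to (104 / 30) × 60 = 208 units per worker

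The width of this range shows that the document does not determine the size.

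**The case against.** The strongest reply is that this is a drafting slip in one bullet. The section names leaders' time in the scope, valuation and perspective sentences, so the intention to count it is plain. That is probably right. A reader might infer that the plan excludes leaders deliberately, or that net benefit will in fact be overstated; the document supports neither. The bias is conditional on the list being complete and followed literally. The list is nevertheless the operative statement of what will be collected, and a mismatch with its own scope is worth correcting before data accrue.

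The second reply is that much of leaders' time is already caught, and this stands in part. Tool 2 activities are carried out with staff, so when done in meetings they can fall under the meetings item. That item also expressly covers planning of deimplementation, which overlaps with Tool 3. Tool 1 is meant to give a fast overview. It would be wrong to infer that leaders' time is not costed at all: the gap is use of the platform outside meetings and collaboratives. That residue is real, since the article describes individual as well as collaborative tools for leaders.

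Third, nothing shows that a cost-effectiveness conclusion would change. This also stands. The article gives no worker, meeting or researcher hours to compare with. It gives no wage figures either, so a reader should not assume that leaders' hours are the costliest in the unit. The point touches the economic evaluation only, not the analysis of the primary outcome.

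**Conclusion.** The point holds as an internal inconsistency with a directional consequence. As listed, the sources leave out leaders' Toolbox use outside meetings and learning collaboratives, although leaders are the intended users and their time lies within the stated cost scope and perspective. If applied literally, incremental net monetary benefit is overstated by exactly the cost of that time at every willingness-to-pay value. The direction follows from the article's own formula and its no-Toolbox comparator.

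The size cannot be established from the document and may be small. The illustrative 180-720 hours, or 0.4-1.6 hours per worker, rest wholly on the assumed one leader per cluster and the assumed 1-4 hours per month. This should be corrected because the direction is known and the correction is cheap, not because a large effect has been shown.

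**What to change.** Extend the log-file item so that it counts the Toolbox minutes of both leaders and health care workers, reported by user role. Confirm that the logs capture user role; the article does not say whether they do. Implementation was scheduled to begin in April 2026, so a reader should not assume that usable trial logs already exist, and role may be hard to recover later if it is not recorded from the start. Add a rule that log time falling inside meetings or learning collaboratives already counted is excluded, so that no hour is costed twice.

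The cost is one changed phrase, a small amount of extra log processing to separate roles and remove overlaps, and a slightly less favourable net benefit. If role turns out not to be captured, adding it is a further task whose cost the document does not allow one to judge.

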A qualitative process evaluation will be performed [13]. Interviews with leaders, health care workers, and informal caregivers conducted in the initial phase of the intervention will be complemented by interviews conducted during and after the intervention period. Additionally, observations will be made during workshops to explore work processes and interactions among participants during implementation of the intervention. To minimize interference with implementation, we will develop standardized informational materials that will be used across all participating units. The researchers will limit their involvement to working directly with leaders through separate workshops and will not be present in the units when the Toolbox is applied in practice. This approach is intended to reduce researcher influence on everyday workflows and ensure that the Toolbox is used as intended by the local leadership. In addition, we will systematically document the contextual circumstances of each unit through context mapping and use standardized observation forms to record events or conditions that may have influenced implementation. These strategies will help differentiate between natural contextual variation and external factors that could interfere with the implementation process.

The data collected will contribute to exploring how the S4R Toolbox supports leaders, how health care workers and informal caregivers experience involvement, and whether capacity-demand challenges improve. In addition, the content of the Toolbox will be explored (eg, comprehension of the learning materials, factors important for sustainability, and levels of engagement and reflection), as well as the nonfunctional and quality aspects of the technical platform (eg, usability, tool design, and accessibility). The knowledge gained will inform further refinements to the Toolbox. Each participating site will include 3-5 focus group interviews with leaders, 3-5 focus group interviews with health care workers (nurses, physicians, and other health care workers), and 10 individual interviews with informal caregivers.

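### The itemised cost data record researcher time only as attendance at local learning collaboratives, which is narrower than the researcher support the EU-funder perspective is meant to cover

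*Protocol article*

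**What the plan says.** The Cost-Effectiveness Analysis section of the protocol article sets the scope of cost: "The costs of the intervention will be based on the time spent by leaders, health care workers, and researchers implementing the S4R Toolbox". It adopts two funder perspectives. The participating organisations carry leaders' and workers' time. The EU is the funder "which covers the costs of researchers’ support for implementing the Toolbox".

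The section then lists the cost data, with a data source for each type of time:

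- Minutes of Toolbox use by health care workers, from log files.
- "Hours that leaders and health care workers spend in meetings discussing the themes of the Toolbox and planning deimplementation or other workplace changes", from collaborative meetings and interviews with leaders.
- "Hours that leaders and researchers spend participating in local learning collaboratives (data source: notes/minutes from the learning collaboratives, including time and participants").

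Recorded time is valued at national wages plus social security contributions.

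The section S4R Intervention Design Development Phase describes who supports implementation. "For each country, a designated intervention team consisting of consortium partners will be formed", and "The teams will be responsible for administering the local learning collaborative and coordinating the overall implementation activities throughout the intervention in their respective countries". The intervention is planned to last 12 months. Local collaboratives are set up in the six European countries, "in addition to 1 principal learning collaborative comprising representatives from all 6 local learning collaboratives".

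The Overview of the Implementation, Evaluation, and Finalization Phase adds: "The researchers will limit their involvement to working directly with leaders through separate workshops".

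**The concern.** The scope statement and the measurement list do not match. The scope is researchers' time implementing the Toolbox. The list measures only their presence at one kind of meeting. Minutes showing the time and participants of a local session cannot show the hours spent preparing it, administering the collaborative, coordinating implementation between sessions, or sitting in the principal collaborative.

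Researcher support is the only cost the section assigns to the EU funder, so this single attendance item supplies the whole EU-side cost. The same section expects the learning collaboratives to influence the Toolbox's effectiveness. The work of running them would then contribute to the measured effect without appearing in the cost. The comparator has no Toolbox, so the uncounted support falls on one arm, and the Toolbox could appear worth funding at a lower willingness to pay than it should.

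**Working it through.** The protocol states no cost total, researcher hours or wage rate, so there is no figure to reproduce. The check compares the listed items with the described tasks, derives the direction of the error, and illustrates its size under labelled assumptions.

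**1. Tasks against listed items**

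| Researcher or team task | Where described | Listed item that captures it |
|---|---|---|
| Attending local learning collaboratives | Cost-Effectiveness Analysis | Third item (minutes) |
| Administering the local collaborative | S4R Intervention Design Development Phase | None |
| Coordinating implementation throughout the intervention | Same | None |
| Principal learning collaborative | Same | None |
| Workshops with leaders | Implementation phase, Overview | Third item if they are local collaborative sessions; otherwise none |

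The log-file item names health care workers only, and the meeting item names leaders and health care workers only. Neither can absorb the missing hours.

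**2. Direction**

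The protocol defines net monetary benefit as effect times willingness to pay (λ), minus cost. Incrementally:

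INMB = λ·ΔE − ΔC

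Let c be the omitted support cost per worker. It arises only in the intervention arm, so the true incremental cost is ΔC + c. Then:

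recorded INMB − true INMB = (λ·ΔE − ΔC) − (λ·ΔE − ΔC − c) = c

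The difference is positive and does not depend on λ. As a numerical check, take assumed values ΔE = 0.5, recorded ΔC = 100 and c = 66.7:

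- λ = 0: −100 recorded, −166.7 true, difference 66.7.
- λ = 200: 0 recorded, −66.7 true, difference 66.7.
- λ = 1,000: 400 recorded, 333.3 true, difference 66.7.

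**3. Which results are affected**

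Researcher support belongs to the EU-funder perspective. The error enters that result and any total that adds the two perspectives. The participating organisations' result contains only leader and worker time, so c is zero there. The SWEMWBS effect estimate is unchanged.

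**4. Illustrative size**

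- From the protocol: 30 clusters of about 30 workers with equal allocation, so 15 × 30 = 450 intervention-arm workers.
- Assumed: 100 to 2,000 unrecorded support hours over the two trial countries, valued at EUR 40 to 60 per hour.
- Low end: 100 × 40 = EUR 4,000; 4,000 / 450 ≈ EUR 9 per worker.
- High end: 2,000 × 60 = EUR 120,000; 120,000 / 450 ≈ EUR 267 per worker.

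The thirtyfold range shows that the documents do not settle how much this matters.

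**The case against.** The strongest defence is that the scope sentence is right and broad enough for all implementation support, that a journal article abbreviates its resource-use list, and that the list does not call itself exhaustive. The fuller economic plan, and the appendices on activities and intervention design, are not shown and may contain the missing item. That is a fair limit on certainty. But the article does more than stay silent: it states what the cost data will be based on and ties researcher hours to a named source that cannot record the other tasks.

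Several stronger readings are tempting and are not supported:

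- **That workshop time is left out.** In its context, separate most naturally means away from the care units. The workshops may be the collaborative sessions themselves, and attendance would then already be counted. The gap in administration and coordination does not depend on this.
- **That net monetary benefit is overstated throughout.** One of the two perspectives contains no researcher cost.
- **That only a small, quantifiable fraction of cost is captured.** Assuming 24 to 60 attended hours and 96 to 384 administration and coordination hours per country, the counted share runs from 24/408 = 6% to 60/156 = 38%. Every input is assumed, and the result is a share of researcher time, not of intervention cost. The omitted hours would be 192 to 768 over two countries, or about 0.4 to 1.7 per intervention-arm worker. How that compares with leader and worker time is unknown.
- **That all the missing hours belong to this trial's intervention arm.** The principal collaborative serves six European countries, of which two are in the cost-effectiveness analysis, so only a share is attributable. Some coordination is also research conduct and is properly excluded.

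Two further points carry some weight. The teams are described as consortium partners, so treating them as researchers is an inference, though the same section places consortium researchers in the collaboratives. And the Toolbox is to be released with self-directed instructions, so routine users may not incur this support. The protocol does not give that as a reason for exclusion, and the trial's effect is obtained with the support in place. It does justify showing the result both ways.

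**Conclusion.** The point holds in a limited form. The itemised cost data fall short of the section's own definition of intervention cost, because administration, coordination and principal-collaborative time have no listed item or source. If the list is followed as written, incremental cost is understated and incremental net monetary benefit overstated by exactly the omitted cost per worker, at every willingness to pay, in the EU-funder perspective and in any combined total.

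This assumes that the intervention teams' work is implementation support of the kind the EU funder pays for, and that no document outside the article adds the item. The size cannot be determined: EUR 9 to 267 per worker is an illustration on assumed hours and rates. No stated threshold is shown to be crossed, since the protocol uses a range of willingness-to-pay values. It is still worth correcting before implementation begins, scheduled for April 2026, because the missing hours cannot be reconstructed later from meeting minutes.

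**What to change.** Add one cost item to the Cost-Effectiveness Analysis section for the implementation-support hours of the Norwegian and Finnish intervention teams:

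- administration of the local collaborative, preparation, and coordination of implementation;
- leader workshops held outside the local collaborative sessions, if there are any;
- an apportioned share of principal-collaborative time, with the apportioning rule stated.

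Name a simple prospective time log, kept from the start of implementation, as the data source. Record research-only hours (interviews, observation, data collection) separately and leave them out of intervention cost. Report the EU-perspective and combined net monetary benefit with the item included, and show the result without it as a sensitivity analysis reflecting self-directed use.

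The cost is minor logging effort for two country teams and a sentence or two in the economic plan. Design, randomisation and outcomes do not change. The downside is a somewhat less favourable net monetary benefit.
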